**11.4 Analysis of Secondary Endpoints**

Median time to progression will be described for each subgroup.

Related toxicities will be described.

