**Subgroup B: DTIC pretreated**

These patients may have received a maximum of two prior lines of chemotherapy, and must have received DTIC or temozolomide.

All patients will be treated with Epothilone B analogue BMS 247550, 20 mg/m2 IV over 1 hour on days 1,8,15 of a 28 day cycle.

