1. OBJECTIVES

1.1 To assess the efficacy of BMS 247550 in stage IV malignant melanoma

1.2 To expand upon the known toxicity profile of BMS 247550 at the recommended phase II dose

1.3 To explore whether there is an association between pharmacokinetics at the recommended phase II doses with the extent of microtubule bundle and mitotic aster formation in peripheral blood mononuclear cells and tumor cells, where available. Total RNA, genomic DNA and total protein will also be extracted and stored from these cells for subsequent molecular analyses.

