**5. EXPECTED ADVERSE EVENTS / DOSE MODIFICATIONS**

**5.1**  **Expected Adverse Events Associated with BMS 247550**

The following adverse events have been associated with BMS 247550:

Common (>20% patients)

- Leukopenia / neutropenia (dose limiting)
- Thrombocytopenia
- Anemia
- Fatigue
- Alopecia
- Myalgia
- Arthralgia
- Sensory neuropathy
- Constipation

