**Reported Adverse Events and Potential Risks:**

Allergic reactions (anaphylaxis)/hypersensitivity (including drug fever), leukopenia, neutropenia, granulocytopenia, sinus bradycardia, edema, hypotension, fatigue (lethargy, malaise, asthenia), fever, alopecia, dermatitis, flushing, pruritus, radiation recall reaction, rash/desquamation, anorexia, constipation, diarrhea, nausea, stomatitis, dysgeusia, vomiting, febrile neutropenia, infection, muscle weakness (not due to neuropathy), dizziness/lightheadedness, insomnia, motor neuropathy, tingling, numbness, speech impairment (dysphasia or aphasia), syncope, arthralgia, myalgia, neuropathic pain, phantom limb pain, post-infection neuralgia, painful neuropathies, pain in extremities, cough, dyspnea, hiccoughs, hypoxia, pneumonitis/pulmonary infiltrates, urinary retention.

Also reported on BMS-247550 trials but with the relationship to BMS-247550 still undetermined: decreased hemoglobin, thrombocytopenia, hyperglycemia, hyperkalemia, hypocalcemia, transaminitis, ataxia, cerebrovascular ischemia (1 case), seizures (1 case).

**Potential Drug Interactions:** BMS-247550 may have a minimal potential to alter the metabolic clearance of drugs that are

highly metabolized by CYP3A4. When BMS-247550 was incubated with human liver microsomes along with compounds

specific for the inhibition of individual cytochromeP450s, significant inhibition was observed only with the CYP3A4 inhibitors

(troleandomycin and ketoconazole) suggesting that BMS-247550 may be a substrate for CYP3A4 in humans.

**Incompatibilities:** Contact of the diluted product with polyvinyl chloride (PVC) equipment or devices that are plasticized

with di- (2-ethylhexyl)pthalate (DEHP) should be avoided to prevent leaching of DHEP into the infusion medium. In order

to minimize patient exposure to DEHP, which my be leached from PVC infusion bags or sets diluted BMS-247550

solutions should preferably be stored in bottles (glass, polypropylene) or plastic bags (polypropylene, polyolefin) and

administered through polyetheylene-lined administration sets or PVC sets plasticized with TOTM (trioctyl trimellitate). IV

sets and components typically used for the administration of paclitaxel have been found to be compatible with infusions of

BMS-247550.

The following infusion components have been qualified for use with BMS-247550**:**

- IV sets containing an in-line 0.22 micron filter
  1. Baxter Vented Paclitaxel Set (Catalog #2C7553)

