**EXPEDITED ADVERSE EVENT REPORTING**

**PHASE II AND III STUDIES WITH INVESTIGATIONAL AGENTS**

**SUPPLIED UNDER CTEP-SPONSORED IND’S**

Expedited Reporting for Phase II Studies (Including hospitalization defined in bullet 1 below)

| **Unexpected Event** | | **Expected Event** | |
| --- | --- | --- | --- |
| **Grades 2 – 3**  **Attribution of Possible, Probable or Definite** | **Grades 4 and 5**  **Regardless of Attribution** | **Grades 1 - 3** | **Grades 4 and 5**  **Regardless of Attribution** |
| Expedited report within 10 working days.  (Grade 1 Adverse Event Expedited Reporting NOT required.) | Report by phone to IDB within 24 hrs. Expedited report to follow within 10 working days.  This includes all deaths witnin 30 days of the last dose of treatment with an investigational agent regardless of attribution.  Any late death attributed to the agent (possible, probable, or definite) should be reported within 10 working days. | Adverse Event Expedited Reporting NOT required. | Expedited report, including Grade 5 Aplasia in leukemia patients, within 10 working days.  This includes all deaths within 30 days of the last dose of treatment with an investigational agent regardless of attribution.  Any late death attributed to the agent (possible, probable, or definite) should be reported within 10 working days.  Grade 4 Myelosuppression or other Grade 4 events that do not require expedited reporting will be specified in the protocol. |

A table showing the expected adverse events associated with BMS 247550 can be found in section 5.1 and in Appendix A.

- For **Hospitalization** only- Any medical event equivalent to CTC Grade 3,4,5 which precipitated hospitalization 9or prolongation of existing hospitalization ) must be reported regardless of expected or unexpected and attribution.
- Telephone reports to the Investigational Drug Branch at [name] available 24 hours daily (recorder between 5pm and 9am EST).
- Expedited reports are to be submitted using AdEERS or the paper templates available at [http://ctep.info.nih.gov](http://ctep.info.nih.gov/). The NCI guidelines for expedited adverse event reporting are also available at this site.
- A list of agent specific expected adverse events (ASAEL) can be found in this protocol.

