**11.5 Reporting and Exclusions**

**11.5.1 Toxicity**

All patients will be evaluable for toxicity from the time of their first treatment with BMS 247550.

- - 1. **Evaluation of response**

All patients included in the study must be assessed for response to treatment, even if there are major protocol treatment deviations or if they are ineligible. Each patient will be assigned one of the following categories: 1) complete response, 2) partial response, 3) stable disease, 4) progressive disease, 5) early death from malignant disease, 6) early death from toxicity, 7) early death because of other cause, or 9) unknown (not assessable, insufficient data). [Note: By arbitrary convention, category 9 usually designates the “unknown” status of any type of data in a clinical database.]

All of the patients who met the eligibility criteria should be included in the main analysis of the response rate. Patients in response categories 4-9 should be considered as failing to respond to treatment (disease progression). Thus, an incorrect treatment schedule or drug administration does not result in exclusion from the analysis of the response rate. Precise definitions for categories 4-9 will be protocol specific.

All conclusions should be based on all eligible patients. Subanalyses may then be performed on the basis of a subset of patients, excluding those for whom major protocol deviations have been identified (e.g., early death due to other reasons, early discontinuation of treatment, major protocol violations, etc.). However, these subanalyses may not serve as the basis for drawing conclusions concerning treatment efficacy, and the reasons for excluding patients from the analysis should be clearly reported. The 95% confidence intervals should also be provided.

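### The one analysis stated for the toxicity endpoint is filtered on an undefined relatedness judgment and could omit or under-count events whose link to the drug the protocol leaves open

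*Protocol*

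**What the plan says.** Section 11.1 lists toxicity as a secondary endpoint without qualification. Objective 1.2 in Section 1 is "To expand upon the known toxicity profile of BMS 247550 at the recommended phase II dose". The analysis given for that endpoint, in Section 11.4, is "Related toxicities will be described".

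The Schema states that "All patients will be treated with Epothilone B analogue BMS 247550", so there is no control group in either subgroup.

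Under Reported Adverse Events and Potential Risks, Section 6.1 gives a second list headed "Also reported on BMS-247550 trials but with the relationship to BMS-247550 still undetermined". It holds nine event types: decreased hemoglobin, thrombocytopenia, hyperglycemia, hyperkalemia, hypocalcemia, transaminitis, ataxia, cerebrovascular ischemia (1 case) and seizures (1 case).

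Section 11.5.1 adds "All patients will be evaluable for toxicity from the time of their first treatment with BMS 247550". An attribution scale ("Attribution of Possible, Probable or Definite") appears in the expedited-reporting table of Section 10.2, and Section 11 does not refer to it.

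**The concern.** Without a comparator, whether an event is related to the drug is a case-by-case judgment that the trial's own data cannot test. If the endpoint is described through that judgment, events set aside as unrelated do not reach the description. Those include the types for which the protocol says the link is unresolved, and these are the types on which a trial meant to extend the toxicity profile could be most informative.

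The background was reported in a similar way. Section 2.2.4 gives percentages for toxicities judged related in the every-three-week study (n=14), and drug-related toxicities for the weekly study. Applying the same kind of filter again limits what this trial can add.

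With *related* left undefined in Section 11, sites could also use different thresholds, so the described rates would depend partly on who made the attribution.

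**Working it through.** The plan gives no figure for this point, so there is none to reproduce. The check is mainly a comparison of sections.

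**1. Does another section supply an analysis free of attribution?**
- Section 11.5.1 sets which patients are evaluable. It does not say which events are described.
- The study calendar collects adverse events on treatment days, before each next cycle and off study, with no attribution limit. That concerns collection.
- Section 10.2 requires expedited reports of grade 4 and 5 events whatever the attribution. It says that events of grade 3 or above leading to hospitalization "must be reported regardless of expected or unexpected and attribution". That is safety reporting and does not describe the endpoint.

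None of these changes the sentence in Section 11.4.

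**2. Which of the nine unsettled event types are really exposed to the filter?** Section 5.1, under the words "The following adverse events have been associated with BMS 247550", lists anemia and thrombocytopenia among events seen in more than 20% of patients. Appendix A lists hemoglobin and platelets as expected. Those two conflict with their place in Section 6.1 and are poor examples of likely omission. The other seven (9 − 2 = 7) are in neither Section 5.1 nor Appendix A: hyperglycemia, hyperkalemia, hypocalcemia, transaminitis, ataxia, cerebrovascular ischemia and seizures.

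**3. How much could be lost?** Let p be the proportion of patients with an event type, q the share of those cases called related, and N the number treated.
- Expected number described = N × p × q
- Chance that at least one case is described = 1 − (1 − p × q)^N

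N is taken from Section 11.3 (23 to 88, that is 11 + 12 to 50 + 38), assuming that treated and evaluable numbers are equal. Neither p nor q is in the document. Both are assumed here: p = 0.10, and q = 1, 0.5 or 0.25.

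| N | q | Expected number described | Chance of at least one |
|---|---|---|---|
| 23 | 1 | 2.3 | 0.91 |
| 23 | 0.5 | 1.2 | 0.69 |
| 23 | 0.25 | 0.6 | 0.44 |
| 88 | 1 | 8.8 | 1.00 |
| 88 | 0.5 | 4.4 | 0.99 |
| 88 | 0.25 | 2.2 | 0.89 |

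For example, with N = 23 and q = 0.5: 1 − (1 − 0.05)^23 = 0.69. The direction is fixed, because related cases are a subset of all cases. The size is not, and at q = 1 nothing is lost.

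**The case against.** A reader might infer three stronger things. The documents do not support them.

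- **That an all-event table is ruled out.** Section 11.4 does not say so. It is silent on such a table, and one could be added from the data collected.
- **That the unsettled events would be omitted.** Section 6.1 describes event types across the drug's trials. It does not decide how a case in this trial is attributed. A doubtful case could be graded possibly related, and the scale in Section 10.2 groups possible with probable and definite. With *related* undefined, such a case might well be described. The supportable statement is that events could be omitted or under-counted.
- **That the trial's safety conclusion is biased in the drug's favor.** That would treat the all-event rate as the true drug effect. In stage IV melanoma without a control arm, all-event rates include harm from the disease, for example liver enzyme rises from liver metastases, or seizures in patients with the stable brain metastases that Section 3.1.8 admits. A filter can understate drug toxicity, and an unfiltered count can overstate it.

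It can also be argued that the protocol uses toxicity to mean drug-caused harm, since the response categories in Section 11.5 separate early death from toxicity, from malignant disease and from other causes. On that usage the wording of Section 11.4 is consistent. Table layout, moreover, is ordinarily left to a statistical analysis plan.

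These arguments limit the consequence but do not remove the point. The protocol makes a stated choice that a later plan would be expected to follow. The choice rests on an undefined term, and Sections 5.1 and 6.1 disagree about the link to the drug for two common events.

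**Conclusion.** The point holds as a weakness in the stated analysis. The description planned for toxicity depends on an undefined attribution judgment that a single-arm trial cannot check, and it could omit or under-count the seven event types identified above. That fits poorly with objective 1.2.

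The size of any under-count cannot be determined from the document. The tabulated figures only illustrate how the filter acts under assumed rates.

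The consequence is limited to how the endpoint is described. The stopping and rejection rules in Section 11.2 use response alone, and collection and expedited reporting are not confined to related events, so nothing is irrecoverable. The change is worth making, but the design does not depend on it.

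**What to change.** Replace the toxicity sentence in Section 11.4 with a statement that:

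- all adverse events in all treated patients will be described by type, worst CTC grade and subgroup, whatever the attribution; and
- a second table will show the related events, with *related* defined, for instance as an attribution of possible or stronger on the scale already in Section 10.2.

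Separately, reconcile the list of unsettled events in Section 6.1 with Section 5.1 and Appendix A on hemoglobin and platelets.

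The cost is one extra table from adverse event data that the calendar already collects. The all-event table will contain disease-related events and should not be read alone as drug toxicity, which is the reason for showing both.

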**11.5 Reporting and Exclusions**

**11.5.1 Toxicity**

All patients will be evaluable for toxicity from the time of their first treatment with BMS 247550.

- - 1. **Evaluation of response**

All patients included in the study must be assessed for response to treatment, even if there are major protocol treatment deviations or if they are ineligible. Each patient will be assigned one of the following categories: 1) complete response, 2) partial response, 3) stable disease, 4) progressive disease, 5) early death from malignant disease, 6) early death from toxicity, 7) early death because of other cause, or 9) unknown (not assessable, insufficient data). [Note: By arbitrary convention, category 9 usually designates the “unknown” status of any type of data in a clinical database.]

All of the patients who met the eligibility criteria should be included in the main analysis of the response rate. Patients in response categories 4-9 should be considered as failing to respond to treatment (disease progression). Thus, an incorrect treatment schedule or drug administration does not result in exclusion from the analysis of the response rate. Precise definitions for categories 4-9 will be protocol specific.

All conclusions should be based on all eligible patients. Subanalyses may then be performed on the basis of a subset of patients, excluding those for whom major protocol deviations have been identified (e.g., early death due to other reasons, early discontinuation of treatment, major protocol violations, etc.). However, these subanalyses may not serve as the basis for drawing conclusions concerning treatment efficacy, and the reasons for excluding patients from the analysis should be clearly reported. The 95% confidence intervals should also be provided.

# APPENDIX A

**Expected Adverse Events Associated with BMS 247550**

| **Category** | **Adverse Event** |
| --- | --- |
| Allergy / Immunology | Allergic reaction / hypersensitivity (including drug fever) |
| Blood / Bone Marrow | Hemoglobin |
| Blood / Bone Marrow | Leukocytes (total WBC) |
| Blood / Bone Marrow | Neutrophils / Granulocytes (ANC / AGC) |
| Blood / Bone Marrow | Platelets |
| Cardiovascular (Arrhythmia) | Sinus bradycardia |
| Cardiovascular (general) | Edema |
| Cardiovascular (general) | Hypotension |
| Constitutional Symptoms | Fatigue (lethargy, malaise, asthenia) |
| Constitutional Symptoms | Fever (in the sbsence of neutropenia, where neutropenia is defined as AGC < 1.0 x 109/L) |
| Dermatology / Skin | Alopecia |
| Dermatology / Skin | Rash / desquamation |
| Dermatology / Skin | Flushing |
| Dermatology / Skin | Pruritis |
| Dermatology / Skin | Radiation recall reaction 9reaction following chemotherapy in the absence of additional radiation therapy that occurs in a previous radiation port) |
| Gastrointestinal | Anorexia |
| Gastrointestinal | Nausea |
| Gastrointestinal | Vomiting |
| Gastrointestinal | Stomatitis / pharyngitis (oral / pharyngeal mucositis) |
| Gastrointestinal | Constipation |
| Gastrointestinal | Diarrhea patients without a colostomy |
| Gastrointestinal | Diarrhea patients with a colostomy |
| Gastrointestinal | Taste disturbance (dysgeusia) |
| Infection / Febrile Neutropenia | Febrile neutropenia (fever of unknown origin without clinically or microbiologically documented infection (ANC <1.0 x 109/l, fever 38.5C) |
| Infection / Febrile Neutropenia | Infection (documented clinically or microbiologically) with Grade 3 or 4 neutropenia (ANC <1.0 x 109/l) |
| Infection / Febrile Neutropenia | Infection with unknown ANC |
| Infection / Febrile Neutropenia | Infection without neutropenia |
| Musculoskeletal | Muscle weakness 9not due to neuropathy) |

| **Category** | **Adverse Event** |
| --- | --- |
| Neurology | Dizziness/lightheadedness |
| Neurology | Neuropathy – sensory |
| Neurology | Neuropathy-motor |
| Neurology | Insomnia |
| Neurology | Speech impairment (dysphasia or aphasia)Myakgua |
| Neurology | Syncope |
| Pain | Arthralgia (joint pain) |
| Pain | Myalgia (muscle pain) |
| Pain | Neuropathic pain (e.g.: jaw pain, neurologic pain, phantom limb pain, posst-infectious neuralgia, or other painful neuropathies) |
| Pain | Pain-Other (Specify) |
| Pain | Tumor pain (onset or exacerbation of tumor pain due to treatment) |
| Pulmonary | Cough |
| Pulmonary | Dyspnea (shortness of breath) |
| Pulmonary | Hypoxia |
| Pulmonary | Hiccoughs (hiccups, singultus) |
| Pulmonary | Pneumonitis/pulmonary infiltrates |
| Renal/Genitourinary | Urinary retention |

Note: The full list of IMT terms is available on the CTEP home page (<http://ctep.info.nih.gov/CtepInformatics/IMT.htm)>.

**A-2**

# APPENDIX B

**Performance Status Criteria**

| **ECOG Performance Status Scale** | | **Karnofsky Performance Scale** | |
| --- | --- | --- | --- |
| Grade | Descriptions | Percent | Description |
| 0 | Normal activity. Fully active, able to carry on all pre-disease performance without restriction. | 100 | Normal, no complaints, no evidence of disease. |
| 90 | Able to carry on normal activity; minor signs or symptoms of disease. |
| 1 | Symptoms, but ambulatory. Restricted in physically strenuous activity, but ambulatory and able to carry out work of a light or sedentary nature (e.g., light housework, office work). | 80 | Normal activity with effort; some signs or symptoms of disease. |
| 70 | Cares for self, unable to carry on normal activity or to do active work. |
| 2 | In bed <50% of the time. Ambulatory and capable of all self-care, but unable to carry out any work activities. Up and about more than 50% of waking hours. | 60 | Requires occasional assistance, but is able to care for most of his/her needs. |
| 50 | Requires considerable assistance and frequent medical care. |
| 3 | In bed >50% of the time. Capable of only limited self-care, confined to bed or chair more than 50% of waking hours. | 40 | Disabled, requires special care and assistance. |
| 30 | Severely disabled, hospitalization indicated. Death not imminent. |
| 4 | 100% bedridden. Completely disabled. Cannot carry on any self-care. Totally confined to bed or chair. | 20 | Very sick, hospitalization indicated. Death not imminent. |
| 10 | Moribund, fatal processes progressing rapidly. |
| 5 | Dead. | 0 | Dead. |

**B-1**

**A**PPENDIX C

Specimen Collection Instructions

**SAMPLING REQUIREMENTS - MOLECULAR STUDIES**

**PRE-THERAPY- (0h cycles 1 and 2)**

1) Peripheral blood mononuclear cells (as cytospins).

Blood is collected into two labeled CPT tubes (Becton Dickinson). Samples are immediately centrifuged at 1000G for 30 minutes and the PBMCs that migrate below the plasma, and above the interface are collected. Alternative methods for harvesting PBMCs are acceptable.

The PBMC pellets are washed twice with 0.5ml 5% FBS in PBS containing 0.02% NaN3. Washed PBMCs are gently resuspended in 0.5ml of 5% FBS in PBS, and the cell number determined from ~0.1 – 0.2 ml of this cell suspension (depending on the concentration of cells), using either a haemocytometer, or a coulter counter. Prepare a cell suspension containing approximately 0.5 X 106 cells/ml. This will be used to prepare cytospins.

(A)Label 10 glass slides (Fisherbrand), and pre-wet each slide by centrifugation at maximum speed for 5 minutes with 50l of 5% FBS/PBS.

(B)Add 100l of cell suspension to each cytofunnel and centriguge at 1000rpm for 10 minutes.

Carefully remove each slide and allow to air dry. Fix the slides in 100% methanol for 5 minutes at -20°C. Air dry and store at 4°C.

(C)Store fixed slides in a tightly sealed container and ship at ambient temperature. Take precautions to ensure that the slides will not break during shipping. Notify personnel in [name] laboratory (this should be done as soon as patients are scheduled for drug infusion): Arrange collection of slides.

SHIPPING ADDRESS: [name]

[name]

Dept of Molecular Pharmacology

Albert Einstein College of Medicine

[name]

Bronx NY 10461 USA

[contact]

[contact]

E-Mail: [[contact]](mailto:[contact])

Please, e-mail or fax the shipping details, including the tracking number, at the time of shipping.

2) Peripheral blood mononuclear cells (as pellet immersed inRNA LaterTM)

PBMCs that are left over from (1) should be resuspended in 5X volumes of RNA Later™, (Ambion). Samples should be stored at 4°C overnight, and shipped at ambient temperature. In the event that refrigeration is not possible, samples should be placed on ice for a few hours prior to shipping.

Notify personnel in [name] laboratory (this should be done as soon as patients are scheduled for drug infusion): Arrange collection of pellets, or same‑day shipment.

Samples should be shipped at ambient temperature.

SHIPPING ADDRESS: [name]

[name]

Dept of Molecular Pharmacology

Albert Einstein College of Medicine

[name]

Bronx NY 10461 USA

[contact]

[contact]

E-Mail: [[contact]](mailto:[contact])

Please, e-mail or fax the shipping details, including the tracking number, at the time of shipping.

3) Peripheral Blood Mononuclear Cells (WHOLE BLOOD).

In the event that PBMCs CANNOT be purified from whole blood (i.e 1 and 2 above cannot be completed), collect whole blood into labeled CPT tubes (Becton Dickinson) 2 X 10mL tubes), and SHIP IMMEDIATELY to

SHIPPING ADDRESS: [name]

[name]

Dept of Molecular Pharmacology

Albert Einstein College of Medicine

[name]

Bronx NY 10461 USA

[contact]

[contact]

E-Mail: [[contact]](mailto:[contact])

Please, e-mail or fax the shipping details, including the tracking number, at the time of shipping. Complete the details of Blood sampling form (next page) and fax to the laboratory.

Laboratory personnel **MUST** be notified in ADVANCE of the SHIPMENT (24hr before), and the shipment MUST be received within 1-2 hrs, to preserve the integrity of the samples.

DETAILS OF BLOOD SAMPLING ON THE BMS 247550 STUDY

*This form should be used only for samples being shipped to the [name] lab for molecular analysis

Patent Name:

Date of Infusion:

Time of Infusion:

Cycle #:

Sampling Time: Baseline Time drawn:

1 hour Time drawn:

24 hours Time drawn

Gauge Needle used:

Vacutainer / Syringe (circle one)

Transport to lab (time deposited to lab):

At room temperature / on wet ice / on dry ice

Peripheral vein / central venous catheter / Picc line

COMMENTS:

4) Tumor biopsies or fine needle aspirates from patients with cutaneous or subcutaneous lesions that area easily accessible for biopsy. No invasive measures will be taken to obtain biopsies. The biopsies will either be a fine needle aspiration or punch biopsy performed in the physician’s office after written informed consent is obtained. No more than three passes with the aspiration or biopsy needle will be done.

- Preparation of slides for Immunohistochemistry(this must be carried out IMMEDIATELY after harvesting, **BEFORE** the sample is immersed in RNA Later™). Prepare 8-10 slides per timepoint.

From biopsy: Imprint the cut tumor surface onto labeled Superfrost plus slides (Fisherbrand): Air dry and fix in 100% methanol for 5 minutes at -20°C. Air dry and store at 4°C.

From fine needle aspirate: Dispense a small aliquot of the aspirate onto Superfrost slides (0.5 X 105 cells): Air-dry and fix as for biopsy. Store fixed slides in a tightly sealed container and ship at ambient temperature. Take precautions to ensure that the slides will not break during shipping.

- Tumor biopsy (core biopsy), or fine needle aspirate immersed in RNA Later

Use the residual tumor material from the preparation of slides.

Immerse sample in 5X volumes of RNA Later™, (Ambion). Store at 4°C overnight, and ship at ambient temperature. In the event that refrigeration is not possible, place samples on ice for a few hours prior to shipping.

SHIP SLIDES AND TUMOR MATERIAL AT AMBIENT TEMPERATURE:

SHIPPING ADDRESS: [name]

[name]

Dept of Molecular Pharmacology

Albert Einstein College of Medicine

[name]

Bronx NY 10461 USA

[contact]

[contact]

E-Mail: [[contact]](mailto:[contact])

Please, e-mail or fax the shipping details, including the tracking number, at the time of shipping.

5) Buccal Cells (cycle 1 only)

The patient should rinse their mouth twice with water to remove particulate matter. They should then swirl approximately 5mL of fresh water in their mouths for a few minutes. The sample should be decanted into a sterile labeled tube and centrifuged at 2500 rpm for 2 minutes to pellet the cells. The cells should then be resuspended in 5X volumes of RNA Later™, (Ambion). Store at 4°C overnight, and ship at ambient temperature. In the event that refrigeration is not possible, place samples on ice for a few hours prior to shipping.

SHIP SLIDES AND TUMOR MATERIAL AT AMBIENT TEMPERATURE:

SHIPPING ADDRESS: [name]

[name]

Dept of Molecular Pharmacology

Albert Einstein College of Medicine

[name]

Bronx NY 10461 USA

[contact]

[contact]

E-Mail: [[contact]](mailto:[contact])

Please, e-mail or fax the shipping details, including the tracking number, at the time of shipping.

